## Method

### Context and design

The TRI-PE project is a randomized controlled trial (RCT) to be conducted in secondary schools within the region of Extremadura. In this region, the academic calendar extends over three terms, from early September to mid-June, with holiday breaks in December–January for Christmas and in March or April for Easter. Specifically, PE is mandatory for all secondary students who attend two coeducational 50-min weekly classes. As illustrated in Figure 1, the intervention will last 10 months, with assessments conducted at three time points: (1) baseline measurement at the end of the first month of the school year (first term, end of September; T1) to ensure that students have had several weeks to a fine-grained picture of the variables under investigation; (2) post-implementation assessment (second term, April; T2); and (3) 2-month follow-up post-implementation at the end of the academic year (third term, June; T3). This study has been approved by the Ethics Committee of University of Extremadura [114/2023] and complies with the principles of the Declaration of Helsinki.

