#### Sample recruitment with inclusion criteria

Between 8–10 secondary PE teachers, assigned to the experimental group and to the control group equally, along a subset of their students, will be anticipated to take part in this study. Given the research team’s limited resources, the maximum number of participating teachers will be set at ten. Randomization will be performed using a digital tool. To minimize the risk of cross-contamination between conditions, teachers from the same high school will not participate. Teachers will be recruited through multiple channels, including social media platforms, telephone calls, and emails. Specifically, information (e.g., flyers and recruitment letters) will be shared via professional networks, PE-related social media groups, and the regional government’s official teacher registry. School principals will also be contacted directly to help disseminate the invitation within their schools.

The registration period will last approximately 2 weeks. Teachers whose participation is not approved by their school leadership will not be included. If more than 10 teachers, or multiple PE teachers from the same school, express interest, a waiting list will be created. Final selection will be based on predefined inclusion criteria and logistical feasibility, including school location, number of participants per school, schedule compatibility, and the research team’s capacity to monitor and support the intervention.

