Teachers must meet the following inclusion criteria to participate in this study: (1) be an in-service PE teacher at the same school for the entire academic year; (2) complete the study questionnaires at three different time points; (3) not participate during the entire academic year in other intervention or training programs similar to this study; (4) attend all the training program sessions; (5) allow research team visits for classroom observation; and (6) participate in a focus group at the end of the intervention. Each PE teacher will recruit at least four classroom groups of no fewer than 16 students each, ensuring that at least 80% of the students in each group participate. Eligible students will be those aged 12–18 years from secondary schools. Participation will be completely voluntary and anonymous. School principals and students’ families will also be informed about the study’s aims and characteristics to obtain their informed consent for participation. The 80% participation rate applies only to baseline (T1); teachers not reaching it may be excluded, with replacements drawn from a waiting list. Dropout over time will not lead to exclusion if at least 60% of students complete all data points. The research team will make every effort to retain the full sample and minimize attrition throughout the study. Finally, the inclusion criteria for students’ participation in the intervention program will be: (1) obtaining consent from both parents/legal guardians and students; (2) commitment to completing the questionnaires assessing the study variables three times; and (3) regular participation in PE lessons.

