#### Blinding

Experienced research assistants, who are postdoctoral staff and trained university researchers, will conduct all data collection. To preserve blinding, they will not have access to group allocation lists, and school codes will be used during assessment. A separate coordinator will schedule sessions to avoid accidental exposure. Teachers, due to their involvement in training, will be aware of their assignment, but not of the study hypotheses. Students will remain unaware of both the hypotheses and their teachers’ group allocation.

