##### First group session

The first group session will address the initial phases of the training (i.e., [1] Get Ready to Work, and [2] How To?), focusing on strengthening teacher relationships, introducing the study’s aims, and familiarizing teachers with the theoretical frameworks underpinning the intervention (i.e., SDT and CMC). First, teachers will report their prior knowledge and experiences with relatedness-supportive and class cohesion strategies, and then complete the questionnaires on the study variables (T1). To introduce theoretical frameworks, teachers will then reflect individually, using color-coded post-its to sort their relatedness-support and class-cohesion strategies into three groups: yellow for consistently used, blue for occasional use, and pink for desired but not yet applied. Subsequently, teacher motivational behaviors (TMBs) related to relatedness-supportive and relatedness-thwarting (Ahmadi et al., 2023, see Supplementary Table 1) and guidelines for promoting task and social cohesion (Leo et al., 2023d, see Supplementary Table 2) will be presented. Teachers’ identified strategies will then be mapped onto these frameworks to facilitate their integration into practical instruction. The session will conclude with a discussion on the benefits of adopting relatedness-supportive practices and class cohesion strategies, followed by assigning a complementary reading to deepen participants’ theoretical understanding before the second training session (Leo et al., 2023d).

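### Unblinded teachers recruit the classes that enter the trial, and the protocol neither says which classes must enter nor fixes them before allocation is disclosed

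*Protocol article*

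**What the plan says.** All of this comes from the Protocol article.

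- **Randomisation.** Under Sample recruitment with inclusion criteria, 8–10 teachers are split equally between the arms. On method, the text says only: "Randomization will be performed using a digital tool". The same sentence that gives the number of teachers says that they come "along a subset of their students, will be anticipated to take part in this study".
- **Class recruitment.** The same section states: "Each PE teacher will recruit at least four classroom groups of no fewer than 16 students each". It continues: "ensuring that at least 80% of the students in each group participate".
- **Replacement.** Also there: "The 80% participation rate applies only to baseline (T1); teachers not reaching it may be excluded, with replacements drawn from a waiting list".
- **Student entry.** Participation is voluntary and needs the consent of parents or guardians and of the student.
- **Knowledge of the arm.** Under Blinding: "Teachers, due to their involvement in training, will be aware of their assignment, but not of the study hypotheses". Students are to stay unaware of the allocation.
- **Calendar.** Context and design puts T1 at the end of September. The section on the face-to-face training phase puts the first two sessions in late September. Experimental teachers complete their own T1 questionnaire within the first group session.
- **Analysis.** The Plan of analysis specifies a 3 × 2 (Time × Condition) repeated-measures MANCOVA. The student covariates are age, sex, sociocultural background and school grade.

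**The concern.** In a cluster-randomised trial, randomisation balances the arms only for what is already fixed when allocation becomes known. Here the teacher is allocated, but the analysed data come from some of that teacher's classes. If classes are settled after the teacher knows the arm, the two arms may be filled by different rules.

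The motives could differ. Experimental teachers must apply the strategies for about six months and are observed in class. Control teachers complete their own questionnaires and change nothing, and the research team administers the student questionnaires with the teacher out of the room. An experimental teacher may therefore have a stake in which classes enter that a control teacher lacks. Cohesion, peer relations and conflict are class features that a teacher can judge before any questionnaire.

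Two things would be at stake: a baseline imbalance between arms, and classes whose expected change differs by arm whatever the training does. With four or five teachers per arm, a few choices can move an arm mean.

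**Working it through.** **Step 1. Is there a window for selection after allocation?**

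| Event | Timing in the article |
|---|---|
| Randomisation | Not dated relative to recruitment of classes or students |
| Choice of classes by the teacher | Not dated |
| Experimental teachers certain to know their arm | By the first training session, late September |
| Student T1 and check of the 80% rule | End of September |
| Replacement of a teacher who fails the 80% rule | At T1 or later; how the replacement gets an arm is not stated |

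Nothing closes the class list before disclosure. Replacement is the clearest route. A replacement teacher enters at about the time when training is under way, and must then bring in at least four classes, possibly for a place whose arm is already known.

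**Step 2. How large could a baseline shift be?** The article gives no figure to reproduce. This is an illustration on assumed inputs:

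- K = eligible groups per teacher, of which four enter (assumed 4 to 10);
- ICC = class-level intraclass correlation of the outcome (assumed 0.05 to 0.20);
- r = correlation between the teacher's judgement and the true class level (assumed 0.3 to 0.8);
- every teacher in one arm picks the classes judged best, and the other arm picks without regard to level.

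Expected shift in student SD = m(K) × r × √ICC. Here m(K) is the mean of the top four of K standard normal values. By simulation, m = 0 for K = 4, 0.293 for K = 5, 0.479 for K = 6, 0.727 for K = 8 and 0.892 for K = 10.

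| K | r | ICC | Shift (SD) |
|---|---|---|---|
| 4 | any | any | 0 |
| 6 | 0.3 | 0.05 | 0.479 × 0.3 × 0.224 = 0.03 |
| 5 | 0.5 | 0.10 | 0.293 × 0.5 × 0.316 = 0.05 |
| 8 | 0.5 | 0.10 | 0.727 × 0.5 × 0.316 = 0.11 |
| 10 | 0.8 | 0.20 | 0.892 × 0.8 × 0.447 = 0.32 |

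**Step 3. Student level.** If 20% of students in one arm stayed out and were exactly the lowest scorers, that arm's mean would rise by φ(−0.84)/0.80 = 0.35 SD. If staying out correlated 0.3 with the outcome, the rise would be 0.3 × 0.35 = about 0.10 SD. The first figure is an extreme bound, because families and students decide on entry and do not know the arm.

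**Step 4. What does the planned analysis remove?** A stable level difference is present at T1 and again at T2, so it largely cancels in the Time × Condition term. Two things do not cancel: classes picked because they look receptive to cooperative work, and classes picked at a low point that later drift back towards their usual level. None of the listed student covariates measures class climate. The figures in Steps 2 and 3 are therefore possible baseline imbalances. They are not estimates of bias in the interaction test.

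**The case against.** The strongest reply is that the article never says classes are chosen after allocation. It dates neither event. Teachers are said to know their arm because they take part in training, which gives no disclosure date. One criterion for the final selection of teachers is the number of participants per school, which could mean that numbers are known at registration, though the phrase is ambiguous. A full protocol may also hold the sequence. This stands: the order is unstated, and recruitment before randomisation is not ruled out.

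A reader might infer that teachers hand-pick individual students. The documents do not support that. Entry rests on family and student consent, and the 80% figure is a minimum participation rate, not permission to leave out a fifth of a class. The reference to a subset of students fits four or more groups out of a larger teaching load.

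The size is also open to challenge. With four eligible groups it is zero. If some experimental teachers preferred easy classes and others troubled ones, the shifts would partly cancel. The absence of an upper limit on classes has no demonstrated direction of effect.

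What the reply does not remove is the rule itself. The article gives class recruitment to someone who will know the arm, states no way of choosing the classes, and allows replacement at T1. That teachers are not told the hypotheses protects little, because the first group session introduces experimental teachers to the study's aims.

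**Conclusion.** The point holds in limited form. The protocol lets teachers who will know their arm recruit the classes, with no selection rule and no stated closure before disclosure, so recruitment bias at class level cannot be excluded. It does not show that such bias will occur, and a reader should not take it as established that teachers choose after learning their arm.

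On the assumptions in the working, the baseline shift from class choice lies between 0 and about 0.3 SD, with about 0.11 SD for four of eight groups, ICC 0.10 and r = 0.5. The top of the range needs strong selection in one direction by a whole arm. It is tempting to read these values as bias in the treatment effect, but T1 in the model absorbs part of a level difference. The part that remains, through differential responsiveness or regression to the mean, is not quantified here. The design should be tightened now, because the choice of classes cannot be repaired after enrolment.

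**What to change.** Amend the section Sample recruitment with inclusion criteria to state the following order:

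1. At registration, each teacher lists every group that meets the size rule.
2. The research team draws four groups per teacher at random, or enters all of them, and fixes the class list before allocation is generated or disclosed.
3. Student and family invitations are identical in both arms, and consent is closed before disclosure where the September calendar allows.
4. Replacement teachers follow the same order, and the text says how they are allocated.
5. The report gives eligible and entered classes and students by arm.

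**Cost.** It takes a few sentences and a random draw. Teachers lose the choice of convenient groups, and allocation may be announced slightly later in September. Closing consent first is the harder part: at least 8 × 4 = 32 to 10 × 4 = 40 groups are involved, and school starts only in early September. If that cannot be done in time, fixing the class list before disclosure still closes the main route.

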#### Blinding

Experienced research assistants, who are postdoctoral staff and trained university researchers, will conduct all data collection. To preserve blinding, they will not have access to group allocation lists, and school codes will be used during assessment. A separate coordinator will schedule sessions to avoid accidental exposure. Teachers, due to their involvement in training, will be aware of their assignment, but not of the study hypotheses. Students will remain unaware of both the hypotheses and their teachers’ group allocation.

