#### Teacher training program

Experimental PE teachers will participate in a training program designed to help them provide relatedness-supportive and class cohesion strategies while avoiding relatedness-thwarting behaviors. The training will be delivered by three experienced researchers in designing and implementing motivational teacher development programs, ensuring a close trainer-to-teacher ratio (~3 trainers per 4–5 teachers) to support implementation quality and fidelity.

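### The blinding statement says teachers will not know the hypotheses, but the training shows the experimental teachers the expected direction of Hypothesis 4, whose questionnaire outcomes are all their own self-ratings

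*Protocol article*

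**What the plan says.** The Blinding section makes a two-part statement about teachers: "Teachers, due to their involvement in training, will be aware of their assignment, but not of the study hypotheses".

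The Teacher training program section says who is trained: "Experimental PE teachers will participate in a training program designed to help them provide relatedness-supportive and class cohesion strategies". The First group session section describes that session as "focusing on strengthening teacher relationships, introducing the study’s aims" and "familiarizing teachers with the theoretical frameworks underpinning the intervention (i.e., SDT and CMC"). Teachers complete the T1 questionnaire early in the session. The theory, the supportive and thwarting behaviours and the cohesion guidelines follow. At the end, "The session will conclude with a discussion on the benefits of adopting relatedness-supportive practices and class cohesion strategies", and a reading is assigned.

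Under Control group teachers and students, control teachers receive no training until after the final assessment and only fill in questionnaires.

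Hypothesis 4 (Aim 2) predicts that by T2 trained teachers will perceive improvement, relative to untrained teachers, in beliefs, feasibility, intention, use of relatedness-supportive behaviours and relationship satisfaction. The Teachers' measures section collects all five by teacher questionnaire.

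**The concern.** A reader of the Blinding section would conclude that teachers know their arm but not what the study expects of them. The training content makes the second half of that hard to sustain for the experimental arm. What can bias a self-rating is knowing the desired answer, whether or not the hypotheses have been read in their numbered form. The training supplies that knowledge to one arm.

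The interpretation of one outcome is at stake above all: self-rated use of relatedness-supportive behaviours. A higher score there would be read as changed teaching. The protocol's Conclusion in fact speaks of raising actual use of these behaviours, which goes beyond how teachers see themselves.

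**Working it through.** No figure in the protocol is at issue, so the check is a comparison of the text.

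1. **What is withheld.** Blinding: teachers are said not to know the hypotheses.
2. **What is given.** First group session: the aims, both theories (SDT and CMC), the target behaviours, and a closing discussion of benefits. Aim 2 predicts improvement in the matters being taught. A teacher who has attended can infer the direction of Hypothesis 4 without seeing its text.
3. **To whom.** Only the experimental arm attends. Control teachers complete questionnaires.
4. **When.** The theory, behaviours and benefits come after the T1 questionnaire. The difference in knowledge therefore opens mainly between T1 and T2. Adjusting for T1 cannot remove it, and in a Time × Condition analysis it would look the same as a programme effect.
5. **Which outcomes are exposed.** The sections on teacher interpersonal behaviour, relationship satisfaction, beliefs, feasibility and intention all use teacher self-ratings. Some items are close to the taught content: the beliefs, feasibility and intention examples all concern promoting positive relationships among classmates.
6. **Whether another source covers the teacher comparison.** The focus group includes experimental teachers only. The Limitations section describes classroom observation for experimental teachers only. Neither gives a control comparison. Students in both arms do rate their teacher's relatedness support and thwarting (Students' measures).
7. **Whether it is acknowledged.** The Limitations section does not list it.

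**Illustration only.** The documents give neither an SD nor a reporting shift. Assume no true effect, a pure reporting shift of d SD between arms, and a two-sided 5% two-sample t-test at T2 (the protocol does not state sidedness). With 8–10 teachers split equally, n = 4 or 5 per arm. The non-centrality is d × √(n/2) on 2n − 2 degrees of freedom.

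| d (assumed) | n = 4: non-centrality | n = 4: chance significant | n = 5: non-centrality | n = 5: chance significant |
|---|---|---|---|---|
| 0 | 0 | 5% | 0 | 5% |
| 0.5 | 0.71 | 9% | 0.79 | 11% |
| 1.0 | 1.41 | 22% | 1.58 | 29% |
| 1.5 | 2.12 | 43% | 2.37 | 55% |

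These are not error rates of the planned analysis, which is a 3 × 2 repeated-measures MANCOVA with covariates. They show only that a shift in reporting can pass for an effect. The point does not depend on them.

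**The case against.** The strongest reply is that aims are not hypotheses. The protocol separates the two, so teachers could be told the aims and still never see Hypotheses 1 to 5. This stands as a matter of wording: there is no flat contradiction. It does not rescue the assurance, because aims, theory and benefits together reveal the direction that Hypothesis 4 predicts.

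Second, the sentence already discloses that teachers know their assignment, and teachers cannot be blinded to training they attend. Both are true. Some reporting bias follows from that alone, and nothing in the documents separates it from the added effect of knowing the direction. The fault is limited to the further assurance and its absence from the limitations.

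Third, changing beliefs, feasibility and intention is a purpose of the programme, self-report is their natural measure, and Hypothesis 4 is worded as what teachers perceive. This stands for those three outcomes. It does not cover self-rated behaviour once that is read as changed practice.

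Two stronger readings are tempting, and the documents do not support them.

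- **Students are also unblinded.** The protocol says "Students will remain unaware of both the hypotheses and their teachers’ group allocation". A reader might set against this that principals and families "will also be informed about the study’s aims and characteristics to obtain their informed consent for participation", and that students must consent too. But that passage does not say what students are told, students do not attend the training, and nothing shows that they learn the hypotheses or their teacher's arm.
- **Control teachers are wholly uninformed.** The recruitment section describes one set of channels and materials for all teachers, and inclusion criteria that mention training sessions and a focus group. Principals are told the aims, and control teachers are offered the same training later. The contrast is between more and less informed teachers.

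**Conclusion.** The point holds for experimental teachers and Hypothesis 4. The stated unawareness of the hypotheses is not effective in the trained arm, the gap favours the programme, and it arises mainly after baseline. A T2 difference in self-rated use of relatedness-supportive behaviours may therefore partly reflect reporting.

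This rests on one inference: that teachers told the aims and led through the benefits can tell which answers are expected. The size of any resulting shift cannot be derived from the documents. The point does not extend to student blinding and shows no difference between arms in consent information. It is worth correcting because it changes what Hypothesis 4 can conclude about practice, but it does not invalidate the design.

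**What to change.** 1. **Blinding section.** Say that experimental teachers know their assignment, the study's aims and the expected benefits, and so are not blind to the expected direction of effect. Leave the student statement as it is.
2. **Limitations section.** Add one sentence for Hypothesis 4: its questionnaire outcomes are self-ratings by unblinded teachers, with the trained arm better informed of the expected direction.
3. **Hypothesis 4, use of behaviours.** Base any conclusion about changed practice on the student-reported relatedness support and thwarting scores, and report the teacher self-rating of behaviour as unblinded and supportive.
4. **Hypothesis 4, beliefs, feasibility and intention.** Keep them as self-report outcomes, labelled unblinded.

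The cost is wording only, since the student scores are already collected in both arms at all three time points. The stated blinding and the Hypothesis 4 claim become slightly less favourable. The conclusion about practice will also share its data with Hypothesis 1, so the two should not be presented as independent confirmation.
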